#### Demographic data

##### Register-based data

Information on age, gender, cancer diagnosis and treatment was obtained from DAHANCA’s national clinical quality database [37] before the nationwide survey was sent out.

##### Self-reported data

Questions on civil status, educational level, occupational status, will be included in the electronic questionnaire at baseline. Questions on current cancer status and participation in other rehabilitation services prior to baseline was included in the nationwide survey. At 3-month and 6-month follow-up information on this will be collected through individual counselling sessions with the clinical dietitian.

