### Participants

Participants will be recruited among respondents of a nationwide survey on late effects and health-related QOL in Danish patients treated for HNC 1–5 years following radiation therapy. The survey population was identified through The Danish Head and Neck Cancer Group’s (DAHANCA) national clinical quality database [37].

The survey was distributed in March 2019. Patients treated for HNC will be eligible for participation in the trial if they meet the following inclusion criteria:

Register-based information:
Have been diagnosed with cancer of the larynx, pharynx, or oral cavityHave completed curatively intended treatment with radiation therapy 1–5 years before survey distribution (1st of March 2014 to 28th of February 2018)Are aged ≥18 years

Self-reported information collected through the survey:
Have no active HNC or any other active cancer at the time for completion of the surveyAre self-reliant. Survey respondents are defined as self-reliant if they answered “Not at all” on the question “Do you need help with eating, dressing, washing yourself or using the toilet?” in The European Organization for Research and Treatment of Cancer’s (EORTC) QLQ-C30 questionnaire [38] on health-related QOLAre able to speak and understand DanishHave confirmed that they are interested in participating in a multidisciplinary residential nutritional rehabilitation programme at specific dates and given their permission to be contacted with further information. This inclusion criterion has been established to obtain permission and contact details for telephone contact and to narrow down the population for inclusion since the nationwide survey was distributed to almost 2000 individuals. By giving survey respondents the possibility to opt out for further contact regarding the trial, we reduce the number of inquiries to each respondent.

Potential recurrence of cancer during the trial will not lead to exclusion of participants. In the event of cancer recurrence in one or more participants, sensitivity analyses will be made to investigate whether this affects the trial results.

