### Intervention

The intervention is a multidisciplinary residential nutritional rehabilitation programme with a primary focus on the physical, psychological and social aspects of eating problems after treatment for HNC. The programme will comprise five days initial residential stay and two days follow-up residential stay after three months (Fig. 1). The rehabilitation centre has developed a core programme model through available evidence and more than 10 years’ experience in offering multidisciplinary residential rehabilitation programmes for heterogeneous groups of patients with cancer [39, 40]. To meet the specific rehabilitation needs of patients treated for HNC, the core programme was further developed through available evidence, patient involvement and a pilot study including 40 patients treated for HNC [4]. Components of the rehabilitation centre’s core programme will be included even though they are not specifically aimed at eating problems. Yet, these activities have shown to be relevant and beneficial to other groups of patients with cancer [39–41]. The programme consists of group sessions with patient education and a few individual activities. The content of these sessions and activities are shown in Table 1 while a detailed schedule of the programme is shown in Additional file 4.

**Table 1 Tab1:** Patient education sessions in the multidisciplinary residential nutritional rehabilitation programme [42] in the NUTRI-HAB trial

SESSION	DURATION (minutes)	CONTENT	SESSION LED BY
Welcome session with presentation of the programme^a,d^	30	The aim of the welcome session is to make participants feel safe and comfortable in the environment in which they will be spending the next five days. This may contribute to increased motivation and willingness to participate actively throughout the programme [43, 44].	Course leader^f^ and clinical dietitian
Presentation round^a,d^	60	In the presentation round, participants will share information about their background and cancer diagnosis, and they will be encouraged to use selected picture cards to narratively describe their expectations and desired outcomes of participation. The aim of the session is to enhance group formation and to establish a sense of community among participants since this may facilitate patient empowerment [45]. Central staff members (course leader, physician, clinical dietitian, and evening hostess) participate.	Course leader

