Social activity^a,d^	60	A social activity including music and movement will be scheduled on the first evening of the programme to support group formation and candidness among participants.	Music therapist
Theoretical session on eating problems^a,d^	105	The session will include dietary advice to manage different nutrition impact symptoms e.g. choice of foods, texture and flavour modification [24, 46]. Exchange of experiences between participants will be encouraged.	Clinical dietitian
Individual dietary counselling^c,d,e^	30 (20 at follow-up)	In the individual dietary counselling, dietary advice will be tailored to the individual participant [24].	Clinical dietitian
Practical kitchen workshop^b,d^	180	In the practical kitchen workshop, participants will prepare foods of different textures and flavours, and take-home recipes will be handed out. The aim of the workshop is to inspire and put theory into practice [4], and practical kitchen sessions have supported dietary changes in studies with other types of cancer survivors [47, 48].	Clinical dietitian
Swallowing exercises^b,d^	90	Participants will be instructed in different swallowing exercises and exercises for jaw and tongue mobility, since these types of exercises may reduce dysphagia and trismus [46, 49]. Participants will receive an exercise manual and a training diary, and will be encouraged to continue doing the exercises, when they come home.	Occupational therapist
Dental problems and oral hygiene^b,d^	75	Dental problems are frequent after treatment for head and neck cancer [22]. The session will include information on how to maintain good oral hygiene and on dental reimbursement rules in relation to cancer treatment.	Dental hygienist
Physical activity^a,d,e^	75	Physical activity may contribute to ameliorate late effects associated with decreased physical function in cancer survivors [50–53]. In the physical activity sessions, participants will be introduced to different kinds of physical activity that they can do at home e.g. balance or resistance training exercises. Exercises will be adjusted to the participants’ training level.	Physiotherapist

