Meaning and values in life^b,e^	90	Optional session. Based on principles of acceptance and commitment therapy [69], the session will aim to support participants in re-establishing meaning in life through reflections on values and sources to meaning in lif e[70, 71].	Psychologist
Individual counselling^c,d,e^	30–45	Individual counselling with relevant health professionals (e.g. speech pathologist, physician) will scheduled depending on participants’ needs.	Depending on need

^a^ Group session with a maximum of 20 participants; ^b^ Group session with a maximum of 10 participants; ^c^ Individual session; ^d^ Session is offered at the initial five days residential stay; ^e^ Session is offered at the two days follow-up residential stay after three months; ^f^ Course leader (nurse, physiotherapist or social worker) coordinates all activities during the week and is the participants’ primary contact person

Rehabilitation Centre Dallund and REHPA, The Danish Knowledge Centre for Rehabilitation and Palliative Care have developed the core model for the residential group-based rehabilitation programme as a best practice patient-centred rehabilitation model for heterogeneous groups of cancer survivors. The rationale, evidence base and content of the model and the specific activities are described in details elsewhere [42]. The core model has been adjusted to meet the rehabilitation needs of the population in the NUTRI-HAB trial

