### Outcome measures and data collection

Outcome measures will be collected at entry, at three, and at six months (Fig. 1). Baseline measurements of the wait-list control group and 6-month follow-up measurements of the intervention group will be performed in one of three regional outpatient clinics depending on the participant’s place of residence. All other measurements will be performed at the rehabilitation centre. Data collected at different time points are shown in Table 2.

**Table 2 Tab2:** Data collection at the different time points in the NUTRI-HAB trial

	TIMEPOINT		
	Baseline	3-month follow-up	6-month follow-up

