### Data analysis

The statistical analysis plan for the trial is shown in Additional file 5. Data will be analysed in SAS® Enterprise Guide® 7.1 by both per protocol and intention-to-treat principle [85]. Data analyses will not be commenced until all data collection is completed. A blinded researcher ([name]) will analyse the data, and the project group will interpret results before unblinding. Development in outcome scores from baseline to 3-month follow-up will be calculated for each participant, and differences between intervention group and wait-list control group will be tested using a two-sample two-sided t-test for normally distributed data and Mann-Whitney U test for non-normally distributed data. A significance level of 5% will be applied. Effect size will be estimated with Cohens d [86]. Multiple linear regression will be used to assess the influence of potential confounding variables (e.g. time interval from completion of treatment) on intervention effect. Mean baseline values for outcome scores in both groups will be presented in result tables. Simple linear regression will be used to test correlations between developments in outcome scores and baseline scores in NRS 2002, MDADI or PG-SGA SF. Sensitivity, specificity and predictive values of different cut-offs in NRS 2002, MDADI or PG-SGA SF at baseline in relation to a clinically relevant improvement in outcome scores during participation in the programme will be assessed. To avoid missing data, participants who drop out of the trial will be encouraged to participate in follow-up measurements. The percentage and patterns of missing values in outcome variables will be examined. If data are missing at random and the percentage of missing data is not substantial [87], multiple imputation techniques will be used in the intention-to-treat analyses.

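### Follow-up cancer status and use of other rehabilitation are tied to dietitian sessions that the described schedule does not give the intervention arm at month 6, nor people who leave or decline the programme but still attend measurements

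*Protocol article*

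**What the plan says.** Two items are at issue: current cancer status and participation in other rehabilitation services.

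- **Before baseline** both come from the recruitment survey, the same source for both arms: "Questions on current cancer status and participation in other rehabilitation services prior to baseline was included in the nationwide survey" (Self-reported data).
- **At follow-up** the same section changes the route: "At 3-month and 6-month follow-up information on this will be collected through individual counselling sessions with the clinical dietitian".
- **Where those sessions occur.** Table 1 assigns individual dietary counselling to the initial five-day stay and to the later two-day stay. The footnote for the latter reads "Session is offered at the two days follow-up residential stay after three months".
- **Where people are measured.** Under Outcome measures and data collection, "6-month follow-up measurements of the intervention group will be performed in one of three regional outpatient clinics". Apart from the wait-list arm's baseline visit, which is also at a regional clinic, all other measurements take place at the rehabilitation centre.
- **What Table 2 expects.** Both items are marked at baseline, month 3 and month 6, as exploratory data, with no distinction by arm.
- **What the data are for.** Participants with recurrence stay in the trial, and "In the event of cancer recurrence in one or more participants, sensitivity analyses will be made to investigate whether this affects the trial results" (Participants).
- **Dropouts.** Under Data analysis, "participants who drop out of the trial will be encouraged to participate in follow-up measurements". Counselling sessions are not mentioned there.
- **General route.** The text after Table 2 says that patient-reported outcomes and other patient-reported data come through REDCap questionnaires sent a week before each measurement, with computer or paper alternatives.

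**The concern.** Data collected inside a treatment session exist only for people who attend that session. The promised sensitivity analysis needs to know who had a recurrence among everyone analysed, including people who stopped the programme but came back to be weighed. If the source is a programme component, ascertainment follows programme attendance and, at month 6, follows arm.

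Two uses are affected. The first is the check on whether recurrence changes the results. The second is the description of other rehabilitation, which matters because the article lets participants use other services freely and says that standard care may vary. An analysis plan cannot recover items that were never collected, so this has to be settled in the data-collection procedure.

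**Working it through.** **The plan's own figure.** Inputs from the Sample size section: mean change 1.74, SD 2.37, power 80%, significance level 5% (two-sided, from Data analysis), withdrawal 15%.

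n per group = 2 × [2.37 × (1.960 + 0.842) / 1.74]² = 29.1, rounded up to 30. Allowing for withdrawal, 30 / 0.85 = 35.3, rounded up to 36. Both figures reproduce, and nothing below changes them.

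**Arm by visit.** The programme is an initial stay and a second stay three months later. The intervention arm therefore has its stays at months 0 and 3. The wait-list arm is offered the programme after month 3, so its stays fall at about months 3 and 6.

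| Visit | Intervention arm | Wait-list arm |
|---|---|---|
| Month 3 | At its follow-up stay: session described | At the centre, then offered the initial stay: session described |
| Month 6 | Regional clinic, programme finished: no session described | At its follow-up stay: session described |

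Table 2 expects both items in all four cells. The described sessions cover three.

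**People outside the programme.** Someone in the intervention arm who leaves before the second stay has no described session at month 3 or month 6. A wait-list participant who declines the programme after month 3 has none at either visit. A wait-list participant who starts and then leaves has none at month 6. All of them may still attend measurements.

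**Size at month 3.** 0.15 × 36 = 5.4 expected withdrawals per arm. The 15% was used to inflate 30 to 36, so it stands for people lost to the primary outcome. The group affected here is people who leave or decline but are still weighed. If the 15% is taken to cover all of them, they are an unknown subset of about 5 per arm.

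**Would one missed case matter?** The article gives no recurrence rate, so rates of 1% to 10% are assumed. Take 6 leavers (36 − 30, the full allowance) with recurrence unrelated to leaving. The chance of at least one recurrence among them is 1 − (1 − p)⁶.

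| Assumed rate p | Expected recurrences per arm of 36 | Chance of at least one among 6 leavers |
|---|---|---|
| 1% | 0.4 | 6% |
| 3% | 1.1 | 17% |
| 5% | 1.8 | 27% |
| 10% | 3.6 | 47% |

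With so few recurrences expected per arm, missing one could alter the sensitivity analysis.

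**The case against.** The strongest reply is that the analysis that matters is intact. The primary outcome is weight change to month 3, and both arms have a described session then. This stands. A reader might infer from the month-6 gap that the recurrence sensitivity analysis of the weight result rests on data from one arm. The documents do not support that.

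Second, silence is not contradiction. The article says where the month-6 measurements are made, not everything that happens there. The sentence on counselling sessions can itself be read as announcing a dietitian contact at month 6, and the dietitians also consult by telephone. The figures and additional files are not shown. This stands in part: it would be too strong to say that the items are not recorded in the intervention arm. What can be said is that no route is described.

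Third, the REDCap rule might already cover these items, since Table 2 lists them as self-reported. But the sentence in Self-reported data is the more specific one and names a different route, so the two need reconciling.

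Fourth, a reader might infer that recurrence drives people out and that cases are therefore lost selectively. The article gives no reasons for leaving and no recurrence rate, so this is an assumption.

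Finally, after month 3 the wait-list arm is offered the programme, so there is no untreated comparison left to protect at month 6. This is correct and lowers the stakes. The article nevertheless plans exploratory long-term analyses, which would lack a described source for these items in one arm.

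**Conclusion.** The point holds in a limited form. The stated follow-up route does not fit the described schedule in two places: the intervention arm at month 6 (36 planned participants), and anyone in either arm who leaves or declines the programme but attends measurements. It also does not fit the general REDCap rule.

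The asymmetry between arms is confined to exploratory month-6 data. At month 3 the remaining weakness is missing information for leavers and decliners who are still weighed. Their number is unknown, and about 5 of 36 per arm is a ceiling that holds only if the 15% withdrawal rate applies to them. Whether those missing would include recurrences depends on assumptions that the article does not inform.

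This is a minor point, worth acting on because the repair is nearly free.

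**What to change.** Reconcile the Self-reported data section with the month-6 visit location, Table 2 and the REDCap rule. Add the two questions already used in the nationwide survey, with the rehabilitation question worded to cover the time since the last visit, to the 3- and 6-month REDCap questionnaire or its computer or paper version. Send it to every participant in both arms, including those who left or declined the programme. Use those answers for the recurrence sensitivity analysis and for describing other rehabilitation, and keep the dietitian session as a supplement.

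The cost is a slightly longer questionnaire on a form that is already sent. It needs no extra visit or staff.

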#### Nutritional risk and presence of nutrition impact symptoms at entry of the rehabilitation programme

##### Nutritional risk screening 2002

The NRS 2002 has been developed and validated to identify admitted patients who will benefit from nutritional intervention [26]. Screening with NRS 2002 comprises a primary screening and, dependent on the result, a secondary screening. The primary screening assesses the presence of recent weight loss, body mass index < 20.5, decreased dietary intake in the preceding week and severe disease. In the secondary screening, the overall score comprises an A-score for nutritional status, a B-score for disease severity and an extra point if aged 70 or above. A higher score indicates greater nutritional risk [26]. Hence, questions on recent changes in body weight and dietary intake will be included in the questionnaire.

##### The scored patient-generated subjective global assessment short form

The PG-SGA SF is a one-page instrument that assesses nutritional risk and nutritional deficit [27]. It includes questions on weight changes, changes in dietary intake (amount or consistency), nutrition impact symptoms and performance status [27]. The PG-SGA SF score ranges from 0 to 36, and a higher score indicates a higher risk of malnutrition. The Danish version has been translated, cross-culturally adapted, and linguistically validated [74]; and is used with permission.

##### M. D. Anderson dysphagia inventory

The MDADI is a self-administered questionnaire on dysphagia-specific QOL in patients with HNC [28]. The Danish version has been translated and culturally adapted, and has been found reliable in terms of internal consistency and test–retest reproducibility [75]. The original version of MDADI consists of 20 items. One item covers overall QOL whereas remaining 19 items form three subdomains: emotional, functional and physical. In addition to a score for each subdomain, a composite score is calculated for the 19 items. The scales range from 20 to 100, and a high score indicates a high degree of functioning. The Danish version contains four additional items concerning specific mechanisms that affect deglutition [75].

#### Rehabilitation needs measured by the REHPA scale

As described under ‘Inclusion and randomisation’, the REHPA Scale is a numerical score of how close or far an individual is from living the life they desire after their disease. The scale ranges from 1 to 9, and a higher score indicate greater rehabilitation needs. In addition to the numerical score, the participant can mark the challenges that prevent them from achieving their goals. Challenges listed in the questionnaire include different practical problems, work-related problems, family problems, physical symptoms, psychological problems and existential problems.

#### Primary outcome

The primary outcome is percentage change in body weight from baseline to 3-month follow-up. Body weight will be measured to the nearest 0.1 kg on calibrated Seca 877/878 scales. In accordance with National Institute for Health Research Southampton Biomedical Research Centre Procedure for Measuring Adult Weight [76], body weight measurements will be continued until three consecutive measurements within 100 g of each other are obtained. The mean of the three will be used in the analyses. Participants will be asked to limit their food and fluid intake two hours before the weighing and to empty their bladder immediately before. For each participant, body weight measurements will be performed at the same time of day (before/after noon) at baseline and 3-month follow-up.

#### Secondary outcomes: patient reported outcome measures

##### Health-related quality of life

Health-related QOL will be measured using the Danish translations of the EuroQol 5D-5 L (EQ-5D-5 L) [77], the EORTC QLQ-C30 [38, 78], and the diagnosis specific EORTC QLQ-H&N35 [78, 79].

The EQ-5D-5 L covers the dimensions mobility, self-care, usual activities, pain/discomfort and anxiety/depression, and a low score indicates a high level of functioning in the given dimension. Overall health is measured with an index score based on the five dimensions and by visual analogue scale (VAS). The index score ranges from − 0.624-1.0 and the VAS scale ranges from 0 to 100. A higher score represents a better self-rated health [77].

Participants’ scores in QLQ-C30 and QLQ-H&N35 will be calculated according to the manual [80]. The tools comprise one global QOL scale, five functional scales and 27 symptom scales. All scales range from 0 to 100, and a high score represents a higher response level. Thus, a high score for a functional scale or global QOL represents a high level of functioning/QOL whereas a high score on a symptom scale represents a high level of symptoms.

